## Abstract

**Background:**

The number of patients with advanced chronic kidney disease opting for conservative management rather than dialysis is unknown but likely to be growing as increasingly frail patients with advanced renal disease present to renal services. Conservative kidney management includes ongoing medical input and support from a multidisciplinary team. There is limited evidence concerning patient and carer experience of this choice. This study will explore quality of life, symptoms, cognition, frailty, performance decision making, costs and impact on carers in people with advanced chronic kidney disease managed without dialysis and is funded by the National Institute of Health Research in the UK.

**Methods:**

In this prospective, multicentre, longitudinal study, patients will be recruited in the UK, by renal research nurses, once they have made the decision not to embark on dialysis. Carers will be asked to ‘opt-in’ with consent from patients. The approach includes longitudinal quantitative surveys of quality of life, symptoms, decision making and costs for patients and quality of life and costs for carers, with questionnaires administered quarterly over 12 months. Additionally, the decision making process will be explored via qualitative interviews with renal physicians/clinical nurse specialists.

**Discussion:**

The study is designed to capture patient and carer profiles when conservative kidney management is implemented, and understand trajectories of care-receiving and care-giving with the aim of optimising palliative care for this population. It will explore the interactions that lead to clinical care decisions and the impact of these decisions on informal carers with the intention of improving clinical outcomes for patients and the experiences of care givers.

## Background

Improving quality of death and access to palliative care is of international concern and in some countries strategies to provide a dignified death in those who are dying have been developed [1–4]. In addition there is a need to ensure those with non-malignant disease have equitable access to appropriate and supportive care services towards the end-of-life [5]. The number of people living with end-stage kidney disease (ESKD) has increased in part due to improved access of an aging population to ESKD care but also due to a higher prevalence of risk factors for chronic kidney disease such as diabetes and hypertension [6, 7]. Worldwide, over 1.4 million people receive renal replacement therapy [8] and the incidence is growing annually by approximately 8 % [9]. In the UK there were 54,824 adult patients receiving renal replacement therapy in 2013 [10]. The mean annual cost of dialysis per patient is estimated at £27 000 [11]. Provision of treatment for ESKD is predicted to consume approximately 2 % of the annual National Health Service budget [12] influenced by disproportionate numbers of older, frailer, dependent patients. Older people with advanced chronic kidney disease have increasing prevalence of co-morbidities [13] and high mortality with a median 2.5 life years remaining for those over 75 years [14]. In addition treatment withdrawal accounts for ∼ 20 % of overall deaths [15]. Evidence is emerging that dialysis may be of little value, in terms of survival benefit and quality of life, to some frailer patients with multiple co-morbid conditions and poor functional status [16, 17]. This has led to questioning of the suitability of renal replacement therapy for ESKD in this population [18] and the impact on quality of life [19].

ESKD includes those patients who have reached stage 5 chronic kidney disease (estimated glomerular filtration rate ≤15 mL/min/1.73 m^2^ as measured using the Modification of Diet in Renal Disease equation (MDRD) formula) [20]. ESKD is a life-limiting condition associated with substantially increased risks of morbidity and mortality. The glomerular filtration may continue to fall in patients with ESKD until a point is reached where dialysis would normally be initiated to maintain life. In a number of renal units in the UK, patients with ESKD are offered an alternative treatment to dialysis or transplantation known as conservative kidney management where a palliative care approach is adopted and supportive care provided by the multidisciplinary team often in liaison with the community team and general practitioner (GP). Deciding when to withhold dialysis in this population and provide conservative kidney management as an alternative requires thorough ethical deliberation and complex decision-making. Some patients may not benefit form dialysis but there is limited evidence to guide patients, carers and staff when making this important decision. There are few service models designed to support this group and little known about how they can be best managed. Ideally, clinicians should be able to accurately distinguish between a patient who will do well on dialysis and a patient who will do poorly; however, any attempt to define such a population has been largely unsuccessful [21]. Some studies have explored age [17], functional status [22], and comorbidity burden [23] as predictors of survival but the development of a criterion score to select people for dialysis has not been developed and individualized assessment is always necessary [24]. Informing that assessment with good quality research centred on patient and carer experiences is still required. When these complex decisions are made, the way in which conclusions are made are difficult to extract, teach and embed in practice. A recent thematic synthesis of qualitative studies [25] described patients with ESKD and their caregiver perspectives on conservative management and end-of-life care and found only five studies [13, 26–29] offering a limited insight into quality of life (QOL) and decision making in those managed without dialysis with no exploration of changes over time. A systematic review of conservative management [30] identified literature in this field as widely distributed and difficult to uncover with database search strategies. Findings were limited and preliminary in nature comparing small groups of patients. Results were not stratified by age or comorbidities and the authors suggest that in patients who opt for non-dialytic management of their kidney disease, guidelines are still required to determine the best clinical practice in this area. There appears to be no studies that explore economic aspects of conservative management in ESKD.

Prospective, randomised trials of dialysis versus conservative kidney management for ESKD are neither ethically justifiable nor practical and therefore only observational studies are available to inform practice [31]. A recent study by Da Silva-Gane and colleagues [32] attempted to compare QOL in patients with advanced chronic kidney disease in those opting for dialysis versus conservative kidney management. This small study, did not investigate clinical decision making, resource use or impact of conservative kidney management on carers. The authors concluded that those opting for conservative kidney management may maintain a better QOL compared to dialysis but higher levels of anxiety were seen in the conservative kidney management patients. The study was limited by major demographic and clinical differences between individuals and the modality groups.

To facilitate improved decision making for individuals with ESKD, accurate information is required for a number of issues including the expected QOL for patients with ESKD, the potential impact a decision not to dialyse may have on the QOL of carers; resource use and costs of conservative care for ESKD and the factors that influence decision making from a patient/carer and health care practitioner perspective [33–36]. Unfortunately there is a dearth of research in this area. The present multicentre study is designed to capture patient and carer profiles when conservative kidney management is implemented and to understand the trajectories of care-receiving and care-giving. It will explore the interactions that lead to clinical care decisions and the impact of these decisions on carers with the intention of improving clinical outcomes for patients and the care giver experience. The economic analysis of conservative kidney management will facilitate greater transparency in relation to resource allocation processes for persons with chronic kidney disease. The purpose of this article is to describe the design of the present study and inform others on the possibilities of performing end-of-life care research in advanced chronic kidney disease. The prospective and longitudinal nature of the design will be discussed. In addition the explanation of the methodology will serve as a comprehensive orientation for the methods section of publications arising from the research.

The aim of the study is to measure and describe longitudinally QOL, symptoms, cognition, frailty and performance in persons with ESKD being managed without dialysis and the impact of these issues on their carers. In addition, the study will analyse decision making related to conservative care for ESKD together with the costs of conservative kidney management.

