#### Carer focused

To measure and describe longitudinally QOL for carers of patients receiving conservative kidney management.To measure and describe the subjective and objective burden of providing informal care in carers, loss of earnings and the opportunity costs of providing such care

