#### Primary outcomes

The mean and 95 % CI for the EQ-VAS will be calculated. Additional exploratory analyses will be used to compare the mean EQ-VAS at 3 months between categories of categorical variables (such as gender, marital status comorbidity) using ANCOVA adjusting for baseline scores. The association between EQ-VAS nd other continuous variables will be investigated using simple linear regression with EQ-VAS at 3 months as the dependent variable. Multiple linear regressions will also be used to investigate associations with comorbidities, age, gender, marital status, severity of symptoms and depression to allow adjustments for confounding. As the study is not powered to detect statistically significant differences in EQ-5D-5L VAS all results will be interpreted with caution. Statistical significance will be assumed for P values 0.05.

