#### Secondary outcomes

Descriptive summaries of patient and carer questionnaire data at 3, 6, 9 and 12 months will be tabulated and presented graphically where appropriate. The number (%) of deaths at 3, 6, 9 and 12 months will be tabulated. Time to death data will be investigated using Kaplan Meier curves. The log rank test statistic will be used to compare categorical variables and Cox proportional hazards model for continuous variables where appropriate.

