#### Economic evaluation

A partial economic evaluation in the form of a cost-outcome description of conservative kidney management will be performed. Each patient’s health and social care resource use and quality of life measurements over the 12 month study period will be collected as stated under Data Collection. Unit costs will be applied to the quantity of resource use for each patient and these will be obtained from national sources where possible. Utilities for the calculation of quality adjusted life years (QALYs) will be obtained using responses on the EQ-5D-5L.

Care-related costs for the carers will also be explored. Multiple regression methods will be used to examine patient and carer factors which are potentially associated with their costs and to adjust for potential confounders. Although the cost effectiveness of conservative kidney management compared with dialysis cannot be established within the current single arm study design, the estimation of the costs and outcomes of conservative kidney management will allow comparisons to be made with similar estimates for dialysis already in the literature.

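### The aim includes the impact of the patient's condition on the carer, but no stated analysis links carer QOL or non-cost burden to the paired patient's state

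*Protocol article*

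**What the plan says.** The aim, at the end of the Background, is to measure and describe over time the patient's QOL, symptoms, cognition, frailty and performance "in persons with ESKD being managed without dialysis and the impact of these issues on their carers". The issues referred to are the patient states just listed.

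The carer objectives (Study objectives, Carer focused) are narrower. The first is "To measure and describe longitudinally QOL for carers of patients receiving conservative kidney management". The second is to "measure and describe the subjective and objective burden of providing informal care in carers, loss of earnings and the opportunity costs of providing such care". Neither mentions the patient's condition.

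The analysis sections then say:

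- Secondary outcomes: "Descriptive summaries of patient and carer questionnaire data at 3, 6, 9 and 12 months will be tabulated and presented graphically where appropriate".
- Primary outcomes: the regressions on QOL concern the patient, for example "simple linear regression with EQ-VAS at 3 months as the dependent variable".
- Economic evaluation: after bringing carers' care-related costs into scope, "Multiple regression methods will be used to examine patient and carer factors which are potentially associated with their costs and to adjust for potential confounders".

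**The concern.** An impact of patient condition on the carer is a relation between two variables, one measured on each member of a pair. A table of carer scores at each visit involves only one of them. The study has a single arm, and the carer's baseline falls after the patient's decision, so there is neither a comparison group nor a pre-decision carer value to set those scores against.

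At stake is a secondary aim. As written, the study can report how carers score and how much burden they describe. It cannot say whether carers of frailer, more symptomatic or more cognitively impaired patients fare worse. The risk is that carer means are later presented as evidence on an impact that was never examined.

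**Working it through.** The documents give no figure for this point, so the check sets each stated analysis against the aim.

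**1. Which stated analyses have a carer outcome, and is the patient's state a predictor?**

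| Quantity | Stated analysis | Links a carer outcome to patient state? |
|---|---|---|
| Patient EQ-VAS at 3 months | Mean with CI, ANCOVA, linear regression | No, the outcome is the patient's |
| Time to death | Kaplan-Meier, log rank, Cox | No, the outcome is the patient's |
| Carer EQ-5D-5L | Descriptive summaries by visit | No |
| Carer subjective and objective burden (non-cost) | Descriptive summaries by visit | No |
| Proxy EQ-5D-5L | Descriptive summaries; inter-rater agreement (Table 2) | No; the pair is used, but to compare two ratings of the patient |
| Costs, carers' included | Multiple regression on patient and carer factors | Yes, though the patient factors are not named |

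Only the cost row links the two sides. Carer QOL and non-cost burden have no such analysis.

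**2. Can by-visit summaries supply the link?** Suppose the carers' scores at one visit were shuffled among the patients. Every carer mean, SD and percentage in the table would stay the same, while any association with the patient's frailty would be destroyed. The table therefore carries no information on that association. Showing patient and carer means side by side over time does not help, because both can drift without any link within pairs.

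**3. Are the data there?** Table 1 schedules the Clinical Frailty Scale, 6CIT, PPS and POS-S Renal in the patient at baseline and at 3, 6, 9 and 12 months. The carer EQ-5D-5L is scheduled at the same five time points. Data collection, Carers, has the burden questionnaire at baseline and 3-monthly. Nothing new need be collected.

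**4. What precision could be expected?** The stated sample size concerns the patient mean only: 100/(1 - 0.10) = 111.1, rounded up to 112. It reproduces, but carers join by opting in and no expected number is given. As an assumption, take 30 to 100 pairs and a true same-visit correlation of 0.3. The 95% CI is tanh(atanh(0.3) ± 1.96/√(n - 3)), with atanh(0.3) = 0.3095:

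- n = 30: -0.07 to 0.60
- n = 50: 0.02 to 0.53
- n = 70: 0.07 to 0.50
- n = 100: 0.11 to 0.47

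These are single-visit figures and only show the order of precision. The value 0.3 is not taken from the documents.

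**The case against.** The strongest case on the other side is that the plan is consistent in itself. The aim is governed by the verbs measure and describe, both carer objectives are descriptive, the carer secondary outcomes include no association with patient state, and the analysis is descriptive to match. On that view the mismatch is one loose word in the aim. The article is also condensed, and an exploratory carer model is something an analysis plan might hold.

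Much of this stands. Objectives and analysis do agree with each other, and rewording the aim would be a legitimate cure. But the aim names which issues are to have an impact and on whom, and even describing that impact requires the two sides to be related. Nor is this simply a detail left out. The article does state how carer questionnaires will be analysed, and it specifies regression where regression is intended.

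Three further objections are sound and limit the point:

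- The questions on burden of care and lost earnings concern caregiving itself, so describing them is some evidence on the carer's situation. It does not show how that varies with the patient's condition.
- A paired model in an uncontrolled cohort yields association only, and a random-intercept slope mixes differences between pairs with changes within them.
- Patients may complete questionnaires with their carer's help, so POS-S Renal may partly reflect the carer's view.

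A reader might infer that carer data are never connected to the patient at all. That is not so: the cost regression has carer costs in scope, and proxy agreement uses the pairing. A reader might also take the other mentions of impact on carers as repeating the same promise. The Abstract and the Background's statement of purpose speak of the impact of care decisions, and the Discussion of impact in general. Only the aim ties impact to the patient's condition.

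**Conclusion.** The point holds for carer QOL and non-cost burden. The aim includes the impact of the patient's condition on carers, the carer objectives drop that link, and no stated analysis restores it outside costs. It is a mismatch between a secondary aim and its analysis. The primary outcome and the patient sample size are untouched.

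No numerical consequence can be derived from the documents, because they give neither the number of opted-in carers nor the variability of carer scores. The precision range above rests on assumed pair numbers and an assumed correlation. The conclusion is also limited to the article as it stands; if an analysis plan already holds a paired carer model, the remedy is to make the article and that plan agree.

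**What to change.** Add to the secondary analysis an exploratory linear mixed model with a random intercept per patient-carer pair, adjusted for visit. The outcomes are carer EQ-VAS/EQ-5D-5L and subjective burden. The predictors are the linked patient's same-visit Clinical Frailty Scale, 6CIT, PPS and POS-S Renal. Report slopes with 95% CIs and call them associations, not causal impact. Keep the descriptive tables alongside. Carer assessments after the patient's death have no same-visit patient measures and stay descriptive. The mode of completion noted on the questionnaire front sheet can be used to check whether the POS-S Renal result depends on carer-assisted responses.

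If the model is not wanted, reword the aim to describing carer QOL and burden, in line with the carer objectives.

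The cost is some analysis wording and a few models on data already scheduled. Four predictors and at least two outcomes give 4 × 2 = 8 or more exploratory slopes on an unknown number of pairs. Intervals may be wide, and the slopes must be read with caution.

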### Study objectives

#### Patient focused

To measure and describe longitudinally patient reported outcomes including QOL, satisfaction in decision-making and costs in patients receiving conservative kidney management (palliative care).To measure and describe longitudinally changes in cognition, frailty and performance in patients receiving conservative kidney managementTo measure and describe the associated health and social care costs of patients receiving conservative kidney management.

#### Carer focused

To measure and describe longitudinally QOL for carers of patients receiving conservative kidney management.To measure and describe the subjective and objective burden of providing informal care in carers, loss of earnings and the opportunity costs of providing such care

#### Renal physicians/clinical nurse specialist focused

To explore the decision making process that precedes referral for conservative kidney management in relation to patient satisfaction in decision making.

## Methods/Design

The research study is a Post-Doctoral Fellowship funded by the National Institute of Health Research in the UK. It is a mixed method study and includes quantitative and qualitative components [37]. In the quantitative component a longitudinal survey of QOL, symptoms, cognition, frailty, performance, satisfaction with decision-making, health service use of patients and associated costs, subjective burden and QOL of carers, loss of earnings and the opportunity cost of providing informal care will be explored. In the qualitative component the decision making process with patients and carers that precedes referral to conservative kidney management will be explored with renal physicians and/or clinical nurse specialists in relation to patient satisfaction in decision making. The longitudinal nature of the study will be explained to participants. Some people may change their mind regarding their selected treatment option and commence dialysis although this is unusual in clinical practice. If this happens the patient and carer data will continue to be collected in order to examine how QOL might increase or decrease with a switch of modality.

The study is multicentre across ten sites in Northern Ireland, England and Scotland. Each site offers conservative management as a treatment option to patients who have reached ESKD. All patients who make the decision not to embark on dialysis will be approached to take part in the study. Their main carer will be asked to ‘opt-in’ to the study with the patient’s consent.

### Study approvals

The study protocol has been approved by the Office for Research Ethics Committees Northern Ireland (ORECNI) (REC reference 14/NI/0057; 14 May 2014) and research governance approval has been granted by the five Health and Social Care Trusts in Northern Ireland and three acute hospital trusts in England, UK with two others in progress in London, England and Glasgow, Scotland. The study is registered with the International Standard Randomised Controlled Trial (ISRCTN) (ISRCTN06857980) [38]. It is sponsored by Queens University Belfast and the Western Health and Social Care Trust, and has been adopted by the Northern Ireland Clinical Research Network (Renal). It is supported by the Northern Ireland Clinical Trials Unit, a UK Clinical Research Collaboration registered clinical trials unit.

